#### Sensitivity Analysis

To examine whether results are biased because of the nonrepresentativeness of the CPCSSN population, we will conduct the analyses on a sample of patients that is representative of the Canadian population based on age, sex, neighborhood socioeconomic status, and rural or urban residence.

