### Variables of Interest

#### Primary Exposure

The primary exposure is the start of the pandemic in March 13, 2020. This date was selected as it marks the beginning of Canadian provincial governments responding to the formal declaration of the pandemic by the World Health Organization on March 11, 2020, by enforcing sweeping public health and safety measures. The prepandemic time frame used is defined as June 22, 2018, through March 12, 2020. The pandemic time frame used in this study runs from March 13, 2020, through December 31, 2022. In addition to comparison between these 2 periods, 30-day interval rates will also be calculated for selected outcomes and indicators where possible.

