#### Analyses of Changes Over Time

We will present the proportions of patients experiencing the outcomes for each time period or mean changes for continuous variables and 95% CIs. Statistical significance of changes from pre to post time period will be assessed using the McNemar test for binary variables, the Wilcoxon signed rank test for original variables, and the paired *t* test for continuous variables. Regression models appropriate to outcome distributions will be used to control for potential confounders of age (<70 vs ≥70 years), sex, count of comorbidities (CPCSSN-validated conditions), neighborhood income quintile, and CPCSSN network (corresponding to location within Canada). Interactions will be examined in the descriptive analysis and will be considered for inclusion in models if they are found to be relevant. We will present adjusted estimates and 95% CIs for outcomes and parameter estimates for the independent variable and covariates. Analyses will be completed using SAS (version 9.4; SAS Institute, Inc).

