### Strengths and Limitations

The strengths of this study include the use of a large, multiprovince primary care EMR data source, developed to understand the epidemiology of chronic diseases and care in Canadian primary care. The data set is regularly updated and includes coded information on most aspects of primary care practice. The relative currency, longitudinal format, and comprehensiveness of CPCSSN data are ideal for the study of practice changes, through time, in response to significant environmental imperatives, such as the sweeping public health measures put in place during the pandemic [41]. Numerous case definition validation studies have been completed [42,43], and the data have also been used to evaluate patterns and quality of health care [19,45]. CPCSSN has undertaken extensive data cleaning algorithms to address data quality issues [41].

There are limitations in this study. EMR data are collected for clinical and administrative purposes and are not primarily collected for research, which may result in incomplete capture of information. Furthermore, participating sentinel clinics are overrepresented by academic practices [59], and by extension, we cannot be certain to what extent the patients in the CPCSSN data differ from other Canadian primary health care patients. There may be issues of nonparticipation bias and variation in data quality. This study will not provide information on people who are not attached to a primary care provider. As with primary care patients generally, older adults and female individuals are overrepresented in the CPCSSN database as compared with the national population; however, as this study is about changes in care patterns, this data set is representative of the population of interest [59]. Clinical context for some research based on secondary use of EMR data can be difficult to infer. Detailed information on family and living circumstances, ethnicity, language spoken, education, and socioeconomic status is rarely captured in EMRs, so it is more difficult to conduct equity analyses, relying instead on neighbor-level indicators.

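### The sensitivity analysis for non-representativeness balances four patient variables but neither clinic type nor network/province, so agreement with the main result would not rule out bias from those two sources

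*Protocol article*

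**What the plan says.** The Sensitivity Analysis section of the protocol article is a single sentence. Its aim is unrestricted, and its method is to repeat the analyses on a comparison sample: "To examine whether results are biased because of the nonrepresentativeness of the CPCSSN population, we will conduct the analyses on a sample of patients". That sample is to be "representative of the Canadian population based on age, sex, neighborhood socioeconomic status, and rural or urban residence".

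Strengths and Limitations names several ways in which the data may not represent the country. At patient level, "older adults and female individuals are overrepresented in the CPCSSN database as compared with the national population". At clinic level, "participating sentinel clinics are overrepresented by academic practices", from which the authors conclude that "we cannot be certain to what extent the patients in the CPCSSN data differ from other Canadian primary health care patients". Nonparticipation and uneven data quality are also mentioned.

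Location appears in two other places. The regression covariates under Analyses of Changes Over Time include "CPCSSN network (corresponding to location within Canada"). The start date is justified under Primary Exposure because "it marks the beginning of Canadian provincial governments responding to the formal declaration of the pandemic".

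**The concern.** A sensitivity analysis can reveal only the imbalances that it changes. This one changes four patient variables. Clinic type and network/province are not among them, and the sample is drawn from the same participating clinics. The stated question, bias from non-representativeness in general, is therefore wider than the comparison can answer.

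The gap falls where the protocol is least sure. It plays down the age and sex imbalance for a study of changes in care. It ties its admitted uncertainty about comparability to the academic practices, which the check leaves out.

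What is at stake is how agreement is read. The abstract frames the conclusions as changes in primary care in Canada, and Dissemination directs them to policy makers. If the two analyses agree, the stated aim invites the conclusion that non-representativeness is not a problem, although two of its possible sources were not tested.

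**Working it through.** The protocol attaches no figure to this analysis, so there is none to reproduce. For scale, Statistical Analysis and Power uses a change from 50% to 55%, that is, 5 points.

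**1. Stated sources against balancing variables**

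| Source | Balanced in the sensitivity sample? |
|---|---|
| Age, sex | Yes |
| Area-level socioeconomic status | Yes |
| Rural/urban residence | Yes |
| Academic practices | No |
| Network/province | No (covariate in the main models only) |

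**2. What the network covariate does.** Study Design specifies a closed cohort, so a patient normally has the same network k before and after. In a linear model with complete pairs, Y = α + β·post + γ(k) + error. Subtracting pre from post removes γ(k). The estimate of β is then the cohort average Σ s(k)·Δ(k), where s(k) is network k's share of the cohort and Δ(k) its change. The national value is Σ t(k)·Δ(k), with national shares t(k). The main effect leaves s(k) in place. Only re-balancing to t(k), or network-by-period terms standardized to t(k), would alter this. Interactions are to be considered only if found relevant, and network is not one of the strata listed under Descriptive Analyses.

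**3. How large a missed bias could be.** With two clinic types, bias = (s − t) × (Δ academic − Δ other), where s and t are the academic shares in the cohort and nationally. If clinic type is unrelated to the four variables, and these do not themselves move the change, the four-variable sample keeps s and hence the whole bias. The same formula applies to an over-represented network. All shares and changes below are assumptions; the protocol gives none. Changes are in percentage points.

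| Scenario | Main | Four-variable sample | National | Bias left |
|---|---|---|---|---|
| A: s 0.4, t 0.2; changes −5 and −10 | −8 | −8 | −9 | 1 |
| B: s 0.6, t 0.2; changes −5 and −15 | −9 | −9 | −13 | 4 |
| C: s 0.3 / 0.5 / 0.7, t 0.1; changes −5 and −15 | −12 / −10 / −8 | −12 / −10 / −8 | −14 | 2 / 4 / 6 |
| D: s 0.5, t 0.1; plus a patient group that is 50% of the cohort and 40% nationally, with an extra −3 | −11.5 | −11.2 | −15.2 | 4.0 |
| E: s 0.5, t 0.2; academic share 0.4 lower in that group, no extra effect | −10 | −9.6 | −13 | 3.4 |
| F: clinic type explained by residence; rural 10% in cohort, 20% nationally; academic share 0.64 urban, 0.24 rural | −9 | −9.4 | −9.4 | 0 |
| G: as F; rural 40% nationally; academic share 0.66 urban, 0.06 rural | −9 | −10.8 | −10.8 | 0 |

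D to G use changes of −5 and −15. Example B: 0.6×(−5) + 0.4×(−15) = −9; 0.2×(−5) + 0.8×(−15) = −13. Example F: the national academic share is 0.8×0.64 + 0.2×0.24 = 0.56, and 0.56×(−5) + 0.44×(−15) = −9.4.

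Over a wider grid of D- and E-type settings, the sensitivity result moved by 0.1 to 0.7 points while the main result was biased by 0.7 to 5.7 points. The movement was away from the national value, but that direction follows from the signs chosen.

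**4. Reading.** Agreement is exact in A to C, small movement hides a larger bias in D and E, and the check works fully in F and G. The protocol does not show which case applies.

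**The case against.** The strongest reply is that the check is sound for what it lists. Age and sex are imbalances that the protocol names, and both are balanced. Rural/urban residence is itself a location variable. The balancing variables stand in the same sentence as the aim, so a reader can see the scope. Academic over-representation is openly disclosed, and nowhere does the protocol say that the sensitivity analysis resolves it. It also asks for caution before firm conclusions are drawn. Practice type may not be recorded: no such field appears among the data sources in Table 1.

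Most of this stands, and it rules out several stronger readings that a reader might infer:

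- That the check is bound to agree with the main result, or has no ability to reveal clinic-level bias. Scenarios F and G contradict this. Re-balancing on residence and area-level socioeconomic status may change the clinic mix.
- That location is ignored. Rural/urban residence is balanced and network is modelled; the gap is the network/province mix.
- That exposure differed by province by design. The protocol's exposure is one date for all patients, and provincial action is only the reason for that date. Different changes by location are plausible but not shown.
- That the results are in fact off by several points. No figure in the documents supports this.

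The reply does not close the gap between aim and method. Disclosing a limitation is not the same as saying that the check leaves it untested, and the covariate for network does not do the work of re-balancing.

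**Conclusion.** The point holds in a limited form. The stated aim is broader than the four balancing variables can serve: the check addresses demographic and rural/urban imbalance, but not academic over-representation or the network/province mix. Agreement with the main result could coexist with bias from either source.

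The size cannot be determined from the documents. The 1 to 6 points in scenarios A to C rest entirely on assumed shares and changes, and exact agreement further requires that clinic type or network be unrelated to the four variables and that these do not themselves move the result. If clinic type does not affect the pre-post change, there is no such bias to miss. The main estimates are unaffected; what needs correction is the reach of the check and the inference drawn from it.

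**What to change.** 1. Add location to the variables on which the sample is drawn or weighted: network, or province where networks can be mapped to it. The protocol gives no such mapping, so it must be established first. Name any province without a network as not covered. Drawing a sample or weighting the full cohort will both serve.
2. Report the pre-post change separately for each of the 13 networks. This shows directly how far the location mix could move a national figure.
3. Restrict the stated aim to non-representativeness in demographics, rural/urban residence and location, and state that agreement does not rule out bias from over-representation of academic practices. Stratifying by practice type is worth adding only if such a field exists, which the protocol does not show.

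The cost is one extra table, external population margins by province, and slightly wider confidence intervals from the added balancing. With 875,934 people in the cohort, that loss of precision should be easy to bear. If only one change is made, the third costs a sentence and removes the unsupported inference.

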### Ethics Approval

This study was approved by the Hamilton Integrated Research Ethics Board on April 11, 2022 (project number 14782-C). Because we will be using deidentified data, no consent is required. This study is also registered with ClinicalTrials.gov (NCT05813652).

## Results

### Study Timeline

The start date of this study was October 5, 2022, and the prospective end date is January 31, 2024. At the time of writing (May 2023), we have finished data cleaning and begun exploratory analyses. As there are known consistencies with CPCSSN data, having a longer exploratory analysis phase has allowed us to liaise with central CPCSSN data managers in order to prepare data for the main analyses. We have now also defined our study cohort: a total of 875,934 individuals between the ages of 18 and 105 years as of 2018 were included.

### Future Analyses

We will attempt to extend our analyses to include the first half of 2022 when data become available if our timelines and resources allow. At the time of writing this protocol (May 2023), data were available up to December 2021. The additional 2022 data will allow us to investigate changes in primary care in the later portion of the COVID-19 pandemic, capturing the Omicron wave, and measure whether any changes identified in the earlier portion of the pandemic were sustained or returned to prepandemic patterns of care.

### Dissemination

We plan to share knowledge products for patients and the public with the patient advisory committee being created as part of the David Braley Primary Care Research Collaborative at McMaster University, with whom several authors are affiliated. *For clinicians*, we will create evidence briefs to be shared with the national and provincial colleges of family physicians through social media and our CPCSSN practice-based research network linkages. *For researchers and policy and practice decision makers* (eg, College of Family Physicians of Canada), we will produce peer-reviewed publications and evidence briefs where we will contextualize the new knowledge against recent research relating to pandemic recovery in health care. The 1- to 2-page evidence briefs will be shared with knowledge users involved in the development and implementation of policies and resources related to pandemic recovery. *For patients*, we will create infographics and a short video that will raise awareness of the issue of chronic condition care gaps and describe patients’ perspectives. These will be circulated via social media and clinical organizations.

## Discussion

### Key Findings

The aim of this study is to help identify signals of change across several domains of primary care, including access, comprehensiveness, and appropriateness, that may have occurred in response to the COVID-19 pandemic. This will be done by investigating the overall number of primary care encounters during the pandemic compared with prepandemic, as well as potential changes in the number of diagnoses addressed during encounters, number of blood pressure measurements, number of vaccines provided, number of blood tests carried out, and so on. Potential changes in indicators specific to the management of chronic conditions will also be investigated, for example, frequency of HbA_1c_ testing for those with diabetes, number and frequency of visits for monitoring of heart failure, and number of prescriptions for diabetes or heart failure. Potential changes in any of these indicators may indicate that gaps in care are present that may benefit from targeted recovery measures.

However, these potential changes in primary care are not inherently negative. For example, many blood tests, examinations, and procedures are considered overused in certain populations and may be conducted more frequently than necessary [53,57,58]. If decreases in number or frequency of these overused tests are identified during the pandemic, this may be considered more appropriate use when compared to prepandemic levels. Furthermore, decreases in frequency of certain primary care interventions may not be clinically significant or necessarily lead to negative health outcomes. Therefore, it is important that each identified change be carefully considered in a broad clinical context before firm conclusions can be drawn.

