## Introduction

The presence of strong primary care systems has been shown to be associated with superior and more equitable health outcomes in the population [1-6]. Core elements of primary care that contribute to population health outcomes include access, continuity, comprehensiveness, coordination, person focus, and equity enhancement [7]. Chronic diseases are common and represent the leading causes of death worldwide [8]. The core elements of primary care make this setting ideal for managing chronic diseases [4,9], and family medicine and other primary care services provide the majority of care for chronic diseases across the lifespan [4,10]. With increasing age, there is an increasing prevalence of multiple chronic diseases [11], and these patients require careful management to reduce morbidity and mortality and improve quality of life [12]. Life-limiting chronic diseases such as chronic obstructive pulmonary disease, heart failure, and chronic kidney disease [13-15] affect millions of people in Canada and are mostly managed in primary care [16-19]. Other conditions that are risk factors for numerous cardiovascular and cerebrovascular diseases (eg, diabetes and hypertension) are associated with poor health outcomes, and these are also managed in primary care [20].

On March 11, 2020, the World Health Organization declared the circulating SARS-CoV-2 as a pandemic. The SARS-CoV-2 pandemic placed a substantial strain on health care services for care of both COVID-19 illness (the majority of which was provided in primary care without need for hospitalization) and non–COVID-19 illness [8,21]. The documented early impacts of the COVID-19 pandemic were reductions in the number of patients visiting primary care offices [22], dramatic increases in remote care especially for older patients [22,23], and new strategies to maintain care such as implementing wellness checks for high-risk patients [24,25].

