Early in the pandemic, there were reductions in visits for chronic condition management [20,26,27], preventive screening and diagnostic testing [28,29], and changes in physician referral behaviors [30]. The limited availability of testing and coordination of prevention services was a concern among Canadian family physicians [31]. Professional organizations recommended continuation of in-person care during the pandemic for complex chronic conditions and when physical examination was required; however, many patients avoided seeking primary care, and clinics experienced decreased attendance relating to the care of serious conditions [32,33]. Although telemedicine strategies can be effective for some chronic disease monitoring, patients who experience lack of equity in access to health care are also likely to experience barriers to using technology [34-36].

The onset of the pandemic worsened existing challenges to the prospects of achieving and maintaining an adequate level of comprehensive primary care in Canada. Understanding the ways in which the core functions of primary care [37-39] were affected by the COVID-19 pandemic is essential for chronic condition management and for system assessment overall. Although there are reports that the volume of primary care in Canada has largely returned to prepandemic levels, it is not clear whether and for whom there is a need to “catch up” on care for chronic diseases. For practices with a tendency for overuse of testing and investigations, these may have declined to more appropriate levels during the pandemic, also highlighting the areas of practice improvement. The objectives of this study are to describe the impacts of COVID-19 on chronic disease care and to determine whether changes were associated with patients’ sociodemographic characteristics and multimorbidity.

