	All patients in our defined cohort; all patients grouped by CPCSSN case definition	Overall number and types of referrals; proportion referred to cardiology, endocrinology (as appropriate for condition)				
**Investigations performed**				Appropriateness		Laboratory
	All patients in our defined cohort	Number of vitamin D, CBC^e^, eGFR^f^, ACR^g^, and liver function tests performed				
	Patients with CKD^h^	Number with and frequency of eGFR and ACR tests				
	Patients without diabetes	Number with HbA_1c_^i^, FBS^j^ measured (screening)				
	Patients taking or not taking statins	Number with and frequency of lipid panel/LDL^k^				
	Patients taking or not taking levothyroxine	Number with and frequency of TSH^l^ measured				
	Patients with the CPCSSN case definition of diabetes	Proportion with HbA_1c_ measured every 6 months and every 12 months				
**Monitoring results**				Appropriateness		Examination
	All patients in our defined cohort; all patients grouped by CPCSSN case definition and age	Proportion with BP ≤140/90 or ≤130/80 (as appropriate based on chronic conditions and age); proportion of patients in the following sBP^m^ ranges: ≤130, 131-140, 141-150, 151-160, and >160				
**Medications**				Comprehensiveness and appropriateness		Medication and risk factor
	Patients with the CPCSSN case definition of diabetes	Proportion of patients with and overall number and frequency of metformin prescriptions, insulin prescriptions, and other oral antidiabetic prescriptions^n^				
	Patients with the CPCSSN case definition of HF	Proportion of patients with and overall number and frequency of β-blocker prescriptions, ARB^o^ prescriptions, and ACE-I^p^ prescriptions				
	Patients who smoke	Number of patients with NRT^q^ prescription				

^a^CPCSSN data table.

^b^CPCSSN: Canadian Primary Care Sentinel Surveillance Network.

^c^HF: heart failure.

^d^BP: blood pressure.

^e^CBC: complete blood count.

^f^eGFR: estimated glomerular filtration rate.

^g^ACR: albumin-to-creatinine ratio.

^h^CKD: chronic kidney disease.

^i^HbA_1c_: hemoglobin A_1c_.

^j^FBS: fasting blood sugar.

^k^LDL: low-density lipoprotein.

^l^TSH: thyroid-stimulating hormone.

^m^sBP: systolic blood pressure.

^n^Other oral antidiabetic medications include classes such as sodium-glucose cotransporter-2 inhibitors, sulfonylureas, meglitinides, dipeptidyl peptidase 4 inhibitors, etc.

^o^ARB: angiotensin receptor blocker.

^p^ACE-I: angiotensin-converting enzyme inhibitor.

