^q^NRT: nicotine replacement therapy.

*Access* to the practice will be measured as the overall number of encounters.

*Comprehensiveness* refers to primary care addressing “all problems in the population (with short-term referral as needed), except those that are too unusual (generally a frequency of less than 1 or 2 per thousand in the population served) for the primary care practitioner or team to treat competently” [1]. As indicators of comprehensiveness, we will measure number of different diagnoses addressed per patient per year, proportion of patients’ chronic conditions addressed at least once a year, number of pneumococcal vaccines and influenza vaccines in patients 65 years or older, and number of prescriptions for nicotine replacement therapy

*Appropriateness* will be examined in 2 ways: laboratory tests that are indicated for monitoring of chronic conditions but may be ordered more frequently than necessary (eg, hemoglobin A_1c_ in diabetics) and laboratory tests that are frequently ordered routinely (or for screening purposes) but may be overused in certain populations, including thyroid function tests, vitamin D, albumin-to-creatinine ratio, and lipid panel testing [53]. We hypothesize that some of these tests, while indicated at a base frequency, may be commonly overused; thus, their frequency may have declined during the pandemic.

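### A fall in suspected-overuse tests may be read as more appropriate use, but no stated estimate separates a selective fall from a general loss of testing

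*Protocol article*

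**What the plan says.** Three places in the protocol article link a decline in testing to appropriateness. The Introduction suggests that, in practices that over-test, tests and investigations "these may have declined to more appropriate levels during the pandemic". Under Outcome Definitions and Measures, the hypothesis is that some tests have a legitimate base frequency but "may be commonly overused; thus, their frequency may have declined during the pandemic". Key Findings then gives the interpretation: "If decreases in number or frequency of these overused tests are identified during the pandemic, this may be considered more appropriate use", relative to prepandemic levels. A caution closes that paragraph: "it is important that each identified change be carefully considered in a broad clinical context before firm conclusions can be drawn".

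Table 1 places the laboratory rows in the appropriateness domain. For the whole cohort, vitamin D, complete blood count, eGFR, ACR and liver function tests are measured as numbers performed. Other rows carry some information on indication: lipids by statin use, TSH in "Patients taking or not taking levothyroxine", eGFR and ACR in chronic kidney disease (CKD), and HbA1c or fasting glucose in patients without diabetes. Encounters are a separate access outcome. The covariates under Analyses of Changes Over Time are age, sex, comorbidity count, income quintile and network.

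**The concern.** The Introduction reports "reductions in the number of patients visiting primary care offices", and early falls in screening and diagnostic testing. If patients were seen less and clinicians ordered as before at each contact, every test rate would fall. The condition in Key Findings would then be met although ordering had become no more selective, and part of the fall would be indicated tests that were missed.

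The article plans evidence briefs on pandemic recovery for policy and practice audiences. A general loss of testing described there as better use could hide part of the care gap that the study sets out to find.

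**Working it through.** **The plan's own figures.** The only design figures are the paired sample sizes of 1276 (correlation 0.2) and 1432 (correlation 0.1) for a change from 50% to 55%. The McNemar formula with continuity correction, assuming two-sided 5% and 80% power, gives 1275.0 and 1431.2, so they reproduce. The present point does not depend on them.

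**Step 1: a general loss of contact.** Tests per patient-year = contacts per patient-year × tests per contact. The article gives neither factor, so assume 4 contacts and 0.10 tests per contact, the latter unchanged. Before: 4 × 0.10 = 0.40. With 10%, 20%, 30% or 40% fewer contacts, the rate is 0.36, 0.32, 0.28 or 0.24. The test rate falls by exactly the loss of contact, whatever values are assumed.

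**Step 2: what a whole-cohort count can show.** Assume 30% of the 0.40 tests are low-value: 0.12 low-value and 0.28 indicated. Three different histories give the same total of 0.36:

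| What was lost | Low-value | Indicated | Total | Low-value share | Ratio of rate ratios |
|---|---|---|---|---|---|
| 10% of both | 0.108 | 0.252 | 0.36 | 30% | 0.90/0.90 = 1.00 |
| Low-value only | 0.08 | 0.28 | 0.36 | 22% | 0.67/1.00 = 0.67 |
| Indicated only | 0.12 | 0.24 | 0.36 | 33% | 1.00/0.86 = 1.17 |

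The planned count is identical in all three rows. In the first row, 0.028 of the 0.04 tests lost (70%) are indicated ones. The last column (low-value rate ratio divided by indicated rate ratio) tells the rows apart.

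**Step 3: significance does not help.** With 875,934 patients and Poisson variance, the fall from 0.40 to 0.36 gives z = 0.04 / √(0.76/875,934) ≈ 43. This ignores clustering and pairing. It shows that the total fell, in all three histories alike.

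**Step 4: the time base.** Step 1 holds for rates or equal windows. Under Primary Exposure the windows are 630 days (22 June 2018 to 12 March 2020) and 1024 days (13 March 2020 to 31 December 2022), although the Abstract speaks of equal periods. A raw total over those windows falls only if the daily rate drops by more than 1 − 630/1024 = 38.5%. With data to December 2021 (659 days), the threshold is 1 − 630/659 = 4.4%.

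**Step 5: two limits on the remedy.** The Introduction reports a large rise in remote care. If remote contacts raised encounters by 10% and testing did not change, dividing the test ratio by the encounter ratio gives 1/1.10 = 0.91, an apparent improvement with no fall in testing. The same 0.91 arises if indicated testing rises 10% while less-indicated testing is flat. So encounters should not be the divisor, and a ratio below 1 is not enough on its own.

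**The case against.** The strongest reply is that the article contains no decision rule. The sentence is an example in the Discussion, is worded as a possibility, and is followed by a caution. The analysis section sets no criterion for appropriateness. This stands: a reader might infer that any fall will be declared an improvement, and the text does not say so. But the caution names no quantity that could separate the two explanations, and Strengths and Limitations concedes that clinical context can be hard to recover from medical records.

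A second reply is that the hypothesis concerns the level of use, not selectivity at each contact. If a test is pure overuse in a group, doing it less is less overuse, whatever the cause. That also stands for such a group. It does not cover the whole-cohort counts, because the article itself grants these tests a base frequency at which they are indicated. Nor is it contradictory for fewer contacts to reduce both access and overuse.

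Third, several Table 1 rows already reflect indication, encounters are collected, and the plan allows interactions to be considered. So it would be wrong to say that the test count is the only input everywhere. What is missing is a stated comparison between strata. An analysis plan that is not shown may contain one, but the printed interpretation does not refer to it.

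Finally, a reader might treat the probability of detecting a non-selective fall as a false-positive rate. It is not: testing really falls in that scenario, so detecting it is correct. The probability also depends on assumptions. For a 5% fall from 10% of patients tested (correlation 0.2), it is about 1.00, 0.62 or 0.24 at design effects of 1, 30 or 100.

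**Conclusion.** The point holds in a limited form. As printed, the favourable reading of a fall rests on test counts or frequencies, and no stated denominator, covariate or contrast separates a selective reduction from a general loss of testing that the article itself leads one to expect. It applies most fully to the whole-cohort counts and less to rows already split by treatment or condition.

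The likely size of any misreading cannot be computed, because the article gives no test rates, no size of fall and no low-value share; the figures above are illustrations. The structural result, that one total is compatible with a lower, equal or higher low-value share, needs only that the count mixes both kinds of test. This is a worthwhile refinement of analysis and wording, not an error that invalidates the planned estimates.

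**What to change.** 1. For tests with an indicated and a less-indicated stratum in or derivable from Table 1, estimate the period-by-stratum ratio of rate ratios with a 95% CI, using rates per person-time. These are TSH by levothyroxine use, lipids by statin use, and eGFR and ACR in patients with versus without CKD (the latter from the whole cohort minus the CKD group).
2. Report the encounter rate ratio beside it as context, not as a divisor, because the mix of remote and in-person contacts changed.
3. Amend Key Findings so that a fall is described as more appropriate use only when testing in the less-indicated stratum actually fell and fell more than in the indicated one. Otherwise, describe it as a reduction in testing that cannot be separated from reduced access. That includes vitamin D, complete blood count and liver function tests, for which Table 1 offers no such strata.
4. State that the strata are proxies, since the article says monitoring tests may themselves be ordered too often.

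The cost is one extra contrast per test from data already planned. The downside is that some declines lose the favourable reading.
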